## Abstract

**Background:**

Patients with mental illnesses often have massive difficulties returning to work after inpatient treatment at a psychiatric clinic and are often at risk of losing their jobs. The psychosocial support for this patient group at the interface of clinic/outpatient care is often insufficient.

**Methods/design:**

The RETURN-study prospectively assesses and surveys 200 patients with mental disorders in a cluster randomized intervention study, i.e. treatment teams and patients from intervention wards receive a return-to-work (RTW) intervention. Patients in control wards obtain treatment as usual (TAU). Pairs of comparable wards (similar patient population, similar staff density) have been identified and then randomized for control and intervention (*n* = 14 for each condition). On intervention wards return-to-work experts (RTW experts) who focus treatment on the workplace-related needs of patients with mental illnesses have been established. These RTW experts ensure the use of available resources within the framework of work-related discharge management and should lead to a more successful return to the workplace.

The days at work in the year after release will be evaluated in a mixed methods approach as well as the return rate in the year after release, disability days in the year after return, relapse rate after 12 months, cost-benefit ratio of the intervention, analysis of the predictors / barriers for a successful return to the workplace (e.g. psychopathology, cognition, stigma, social-psychiatric support, company support, etc.), possibilities to implement the concept of RTW experts in standard psychiatric care (TAU - treatment as usual), the impact of the RTW experts’ approach on the treatment process in standard psychiatric care.

**Discussion:**

This approach is already internationally established in the field of somatic rehabilitation and supported employment [Am J Psychiatry 171:1183–90, 2014; Lancet 370:1146–52, 2007; Cochrane Database Syst Rev, doi:10.1002/14651858.CD006237.pub3, 2014]; the innovative aspect of this project is to implement and evaluate it in standard psychiatric care in Germany. This project requires no new interventions to be developed and tested, as the techniques of the case manager/job coach is applied to the field of return to work.

**Trial registration:**

The study was registered in Deutsches Register Klinische Studien searchable via its Meta-registry (http://apps.who.int/trialsearch/), Trial registration number: DRKS00016037, Date of registration: 21/12/2018, URL of trial registry record.

## Background

Mental illnesses are among the most common diseases worldwide. In Germany, 28% of the population aged 18–79 have suffered from a mental illness within the last 12 months [1]. Accordingly, cases of inability to work caused by mental illness are high. In particular the days of inability to work have been increasing in recent years. Mental illness is now the third most frequent diagnostic group for sick leave or inability to work [2, 3]. The consequences for health insurers, companies and national economy are expenditures in billions of Euro, not including the additional indirect costs, especially for early retirement. Yet, mental illness is the most common cause of early retirement in Germany [4].

Mental illness and the ability to work interact in many different ways. Therefore, many patients with severe mental illness (e.g. schizophrenia or bipolar affective disorder) do not manage to find and keep regular employment. In addition, the number of cases of mental illness (usually depressive disorders) in Germany have risen for years as have the days absent from work [5, 6].

On the other hand, work and employment may have positive effects on the course of illness [7–9]. There is an undisputable salutogenetic aspect of work [10]. Work in general has a beneficial effect on health. Randomized studies demonstrated that mentally ill people who were supported as early as possible in their job search and in returning to work succeed more often than patients undergoing a long rehabilitation phase first [11]. In addition, these studies showed that permanent employment (competitive employment) increases quality of life and reduces hospital days [12].

Accordingly, obtaining and maintaining jobs for people with mental illness is challenging on the one hand and an important prerequisite for a good prognosis on the other. A loss of employment due to mental illness is not only associated with negative consequences for those affected (i.e. missing day structure), but is a serious societal problem as well, due to resulting follow-up costs (sickness benefits, unemployment benefits, reduced social contributions etc.)

### Acute psychiatric crises, inpatient treatment and return to work

A particularly vulnerable time is that of an acute mental health crisis, which requires inpatient hospital treatment. It tears those affected out of their employment relationships, sometimes over longer periods of time. A successful reintegration of those patients after the acute episode of illness would therefore be an important prognostic factor for the further course of the disease. A failed reintegration in contrast would be a high risk factor for longer incapacity to work, long payment of sickness benefit, unemployment and a less favourable course of the disease.

Present data shows that it is a frequent health (or social) problem. In 2010 about 800,000 psychiatric inpatient cases were documented in Germany [13]. About 20% (= 160,000 people) of these cases were working patients [14]. Up to 30% of these patients did not return to work after discharge from hospital [14] and of those returning it was unclear how long they were able to successfully resume their employment relationships. Considering the related social decline and associated reduction in participation in social life, these numbers are alarming [15, 16].

### Reasons for unsatisfactory return to work after psychiatric inpatient treatment

Reasons for the frequent job losses after inpatient psychiatric treatment are multifactorial and often mutually dependent. In particular, awareness for aspects of work is often too low in the context of psychiatric in- or out-patient treatment. Furthermore, the lack of support of those affected when returning to work, the dealing with the disease, especially in the context of work, as well as how employers deal with the affected people or the working conditions may play a role. In the context of psychiatric inpatient treatment, the salutogenetic effects of work are given too little consideration. The fact that returning to work can not only be a treatment goal, but also a therapeutic action, is often neglected in the reality of psychiatric care. Currently, a corresponding formalized procedure is insufficiently integrated into the processes of psychiatric hospitals.

Psychosocial counselling and support are also part of the treatment of the disease, especially with regard to the return to work process. Although the current German S3 guideline “Psychosocial therapies for severe mental disorders” emphasizes the importance of the return to work process for the patients, many clinics often fail to appropriately prepare patients for routine reasons [17]. Established support such as re-entry counselling and structured reintegration measures (e.g. BEM, gradual reintegration) are currently only implemented for a fraction of patients and, above all, are not supported across the various interfaces [14]. As a result, the return to work remains fearful for many patients [14, 18] and the actions that may be initiated in the clinic may not be continued after discharge from inpatient care.

### Aim and research questions

The aim of the planned project is to establish a psychosocial case-management intervention (return-to-work-experts) that supports patients at the interface between inpatient treatment and return to work and to estimate its effects in a cluster-randomized study.

We presume that the intervention (return-to-work-experts, details see methods) will optimize care of the affected patients with regard to improving their return to work, thereby focusing on the interface between in-patient treatment and outpatient care (“occupational discharge management”). The chain of action on the structural and the individual level is visualized in Fig. 1.

**Fig. 1 Fig1:**
[figure not shown]
German terms and their translation: BEM = Betriebliches Eingliederungsmanagement (Corporate integration management), Stufenweise Wiedereingliederung (gradual reintegration)

We expect improvements in the number of patients who will be able to return to work and also in the number of days at work in the year after release from hospital. This could also result in substantial economic savings (for example, sickness benefit, loss of productivity, etc.). Mediators of these expected improvements are increased numbers of patients for whom specific supportive measures (e.g., work therapy, gradual reintegration, BEM processes, etc.) are initiated. We assume that the proposed intervention primarily will increase the implementation of measures already existing in routine care and will help to overcome the interface problem at the time of inpatient discharge.

## Methods

### Study design

The study is designed as a multi-center, cluster-randomized controlled trial in acute psychiatric wards addressing inpatients suffering from a psychiatric disorder. RTW-experts will be introduced on wards chosen for the intervention, while on control wards treatment as usual will be continued.

### Setting and participants

The study will be implemented on *n* = 28 acute wards (=clusters) in seven psychiatric hospitals in the greater Munich area. Eligibility criteria for the wards to be included are: acute psychiatric ward in one of the participating hospitals, patients with psychiatric disorders are commonly treated on these wards.

All patients treated on these wards and on admission to the ward, each patient fulfilling the inclusion criteria will be consecutively offered participation in the trial.

#### Inclusion criteria

· Age 18–60 years.

· Diagnosis of a mental illness [ICD-10 Chapter F2–4, F6 (we assume that the majority of patients with existing employment relationships suffer from an affective disease [14]).

· In a contractual employment relationship, in which they can be reintegrated.

· Psychopathologically capable of reflecting on work in general and on their own work.

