#### Primary outcome

The scientific rationale is that the establishment of return-to-work (RTW) experts for inpatient mental health patients focuses on the workplace needs of these patients, leading to a better usage of existing resources as part of a work-related discharge management, and thus to a more successful return to the workplace.

The primary objective is to display this improved return to the workplace after in-patient psychiatric care as a group difference (intervention vs. control) using days in work and days of incapacity to work during 1 year after discharge from hospital.

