### Sample size calculation and statistical analysis

The aim is to obtain a sample of *n* = 28 clusters (i.e. psychiatric acute wards) with a total of 200 patients (8–10 per cluster). For this, about 2000 patients need to be screened (Mernyi et al., 2018).

In order to be able to demonstrate a significant result with a power of 80% assuming a small to medium effect size (0.5), a total sample size of 128 patients is required (two-sided independent samples t-test, α = 0.05). With regard to expected drop-outs (drop-out rate 30–40%), this minimum number of cases is planned to be exceeded by 72 patients. Thus, a total of 200 patients are to be included (100 in each group).

The primary analysis will be a comparison of days in work at T4 between the intervention and control groups. To assess the effect of the intervention on the continuous primary outcome, a random effects linear regression model will be fitted with ward (cluster) as a random effect term and intervention group as a fixed effect. The point estimate for the intervention effect will be reported together with the corresponding 95% confidence interval. A *p*-value < 0.05 will be considered as providing statistical significant evidence of a group difference. A per protocol approach will be taken to the analysis, i.e. patients in intervention clusters will be analyzed in this group, if they had contact with the RTW-expert at least once during their inpatient stay and once after discharge.

Exploratory analyses will be performed to assess the effect of the intervention on the secondary outcome measures. Random effect linear models will be fitted to the continuous secondary outcome measures, analogous to the primary analysis. For binary secondary outcome measures, logistic regression models using GEEs will be fitted.

The health economic analysis is based on the net benefit approach. To analyze the cost-effectiveness of the RWT intervention, the incremental cost-effectiveness ratio (ICER) is determined for gaining a QALY compared to routine treatment. The estimation of ICER stochastic uncertainty is done by nonparametric bootstrapping and the determination of the cost-effectiveness acceptance curve [29].

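### The primary model for days in work has no term for contracted working days per week although eligibility sets no contract size, which costs avoidable precision but does not bias the comparison

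*Protocol article*

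**What the plan says.** The inclusion criteria require the patient to be "In a contractual employment relationship, in which they can be reintegrated". No minimum hours or days per week are set.

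The Primary outcome section frames the objective as a group difference "using days in work and days of incapacity to work during 1 year after discharge from hospital". The section on sample size and analysis then fixes the variable: "The primary analysis will be a comparison of days in work at T4 between the intervention and control groups". It also states the model: "a random effects linear regression model will be fitted with ward (cluster) as a random effect term and intervention group as a fixed effect". No denominator, offset or covariate for contracted days is named.

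Randomization and blinding lists patient numbers, diagnoses and staffing among the features used to pair wards. Contract size is not named. Table 1 records the employment relationship at T0. It lists days at work, days of incapacity and days of partial return as separate items at T2 to T4.

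The sample size rests on a t-test ("two-sided independent samples t-test, α = 0.05") at an effect size of 0.5, which gives 128 patients, raised to 200 for drop-out. No standard deviation or difference in days is given.

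**The concern.** Take a patient contracted for 3 days a week who returns at once and misses nothing. That patient reaches 3/5 = 60% of a five-day patient's maximum, the same count as a five-day patient absent for 40% of the year. On a plain day count, a complete return and a substantial failure look alike at patient level.

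Contracted days per week at T0 are settled before the intervention and carry no information about its effect. Left out of the model, they enlarge the residual variance. With 14 wards per arm and about 7 patients per ward (200/28), any chance difference in contract mix passes into the estimate unadjusted. What is at stake is the precision of the primary result, which could be recovered at almost no cost.

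**Working it through.** **1. The plan's own figure.** An exact two-sided t-test with effect size 0.5, α = 0.05 and 80% power needs 63.8, so 64 per arm and 128 in total (power 0.801). The rise to 200 corresponds to 72/200 = 36% drop-out, inside the stated 30–40%. Both figures reproduce.

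**2. Set-up.** Write days in work as D = C × F, where C is contracted workdays in the year and F is the share of them worked, independent of C. Let the effect be proportional to contracted days. Then

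CV²(D) = (1 + CV²(F))(1 + CV²(C)) − 1,

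and the effective sample for the raw count, relative to analysing F, is CV²(F)/CV²(D).

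**3. Inputs.** These are assumptions, because the article gives no contract mix and no standard deviation:
- 220 workdays in a full-time year.
- 20–40% of patients part-time at 2.5, 3 or 4 days a week.
- 20–30% never return (the Background cites up to 30%). For the rest, F is uniform on 0.3 to 1.

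**4. One case in full (30% no return; 20% part-time at 3 days).**
- E(F) = 0.7 × 0.65 = 0.455.
- E(F²) = 0.7 × (0.65² + 0.7²/12) = 0.324, so CV²(F) = 0.324/0.455² − 1 = 0.567.
- E(C)/220 = 0.8 + 0.2 × 0.6 = 0.92 and E(C²)/220² = 0.8 + 0.2 × 0.36 = 0.872, so CV²(C) = 0.872/0.8464 − 1 = 0.030.
- CV²(D) = 1.567 × 1.030 − 1 = 0.614. The ratio is 0.567/0.614 = 0.92.

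**5. Range.** For the linear model adjusted for C, the residual variance is E(C²)Var(F), so its ratio on the same basis is 1/(1 + CV²(C)).

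| Part-time share and days | Raw, 30% no return | Raw, 20% no return | Adjusted for C |
|---|---|---|---|
| 20%, 4 days | 0.98 | 0.97 | 0.99 |
| 40%, 4 days | 0.97 | 0.96 | 0.99 |
| 20%, 3 days | 0.92 | 0.90 | 0.97 |
| 40%, 3 days | 0.87 | 0.83 | 0.95 |
| 20%, 2.5 days | 0.88 | 0.85 | 0.95 |
| 40%, 2.5 days | 0.79 | 0.74 | 0.91 |
| any share, shorter hours on all 5 days | 1.00 | 1.00 | 1.00 |

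The raw count loses about 2–26% whenever fewer days are worked, and nothing when only hours are shorter. The covariate recovers roughly 60–70% of the loss.

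**6. Chance imbalance.** A 10-percentage-point difference between arms in the part-time share shifts the raw difference by 0.10 × (220 − part-time year) × E(F). At 3 days (132-day year) and E(F) = 0.455 this is 0.10 × 88 × 0.455 = 4.0 days. At 2.5 days (110-day year) and E(F) = 0.52 it is 0.10 × 110 × 0.52 = 5.7 days. The SD of D is about 64–72 days in these cases, so with 64 per arm the standard error is about 11–13 days (SD × √(2/64), clustering ignored). The shift is therefore at most about half a standard error. For part-time shares of 10–50%, an intraclass correlation of part-time status of 0–0.1 and 128–200 patients, the chance SD of such an imbalance is about 4–10 percentage points.

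**The case against.** **Bias.** A reader might infer that the comparison partly measures contract size instead of return to work. The documents do not support that. Contract size precedes the intervention and wards are randomised within matched pairs, so its expected contribution to the arm difference is zero. The shift in step 6 is also not an extra error on top of the variance: it is how that variance shows itself, and the confidence interval already covers it. The analysis set is restricted ("A per protocol approach will be taken to the analysis"), with a contact condition stated for the intervention arm, and there is no blinding. A systematic difference in contract mix is therefore conceivable, but nothing in the article shows one.

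**Power.** A reader might also infer that power falls below the planned 80%, to about 68–77% at 2.5–3 days a week. That requires the 0.5 to refer to the share of contracted days. The article says only "with a power of 80% assuming a small to medium effect size (0.5", next to a primary analysis of days in work. The natural reading is 0.5 SD of that outcome, whose SD already contains contract variation.

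**Outcome.** Absolute days are a defensible target: the aims section links more days at work to economic savings, and time to partial or full return is a separate secondary outcome. Replacing the count by a ratio is debatable, because contracts can end or change during follow-up.

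**Definition.** The article does not define a day at work, and a full protocol may do so.

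All four points stand and limit the finding. They leave untouched that the stated model omits a baseline variable likely to be strongly related to the outcome.

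**Conclusion.** The point holds as a matter of precision. As stated, the primary analysis uses an unscaled number of days, with arm as the only fixed effect, in a population with no limit on contract size. The inclusion criterion itself is not wrong; the gap lies in the outcome and model text.

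The loss runs from nil (shorter hours on all weekdays), through about 2–4% of the effective sample (4 days a week), to about 8–26% (2.5–3 days a week). These figures depend on the assumed contract mix, the distribution of the share worked and an effect proportional to contracted days. None of these is given in the article. No bias in expectation and no error in the sample size calculation follows. The change is worth making because it is cheap.

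**What to change.** Keep days in work as the primary outcome. Add contracted working days per week, fixed at the T0 value, as a baseline covariate in the primary ward random-effects model. Take it from the T0 employment item, or add one question if it is not recorded there.

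As a supporting analysis, show days in work as a share of T0-contracted days, also expressed as full-time-equivalent days. Fix the denominator at T0 so that later job loss or a contract change does not alter it. The share can then exceed 100% if contracted days increase, which should be noted when it is reported.

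Cost: at most one T0 item and one more model term. No additional patients or visits are needed.

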#### Exclusion criteria

· Cognitive impairment.

· Insufficient proficiency in German language.

· Main diagnosis of an organic mental disorder (F0), substance abuse (F1) or an eating disorder (F5).

#### Randomization and blinding

We will determine pairs of comparable wards (number of patients, distribution of diagnoses, staff etc.) and then randomize one ward of each pair to the intervention and one ward to the control condition. While the principal investigators will determine the paired wards, the statistical institute of our department (IMedIS) will do the randomization.

Randomization takes place at cluster level (*n* = 14 wards each to the intervention group or control group) to minimize contamination effects [19].

As to the nature of the intervention (implementation of RTW-experts) there will be no blinding.

To avoid selection bias, all patients fulfilling inclusion criteria will be recruited consecutively in the intervention and control group. This process is monitored by the study center and will be reported in form of a CONSORT diagram. There will be special emphasis on documenting how many patients (and for what reasons) did not consent to participate in the trial.

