### Data collection

The same data at the same time points will be collected in the intervention and control group (Table 1). Data collection will take place at five times during the inpatient stay and after discharge.

**Table 1 Tab1:** Planned data collection

	T0 (shortly after admission to hospital)	T1 (shortly before release from hospital)	T2 (3 months after release)	T3 (6months after release)	T4 (12 months after release)
Patient					
Demographics including information on					
School and vocational training	x				
Employment relationsship	x				
Business, enterprise (industry)	x				
Business, enterprise (size)	x				
Motivation	x	x	x	x	x
Anxiety, confidence	x	x			
Days of incapacity to work	x		x	x	x
COPSOQ	x			x	
COPSOQ (additional information)	x				
Self-stigma of mental illness scale short form – self-concurrence	x	x		x	
Cognitive appraisal of stigma-related stress	x	x		x	
Questions concerning disclosure of the disease at the workplace including					
Questions on the decision-making phase	x	x		x	
Questions on the decision to disclose	x	x		x	
Questions on the attitude towards disclosure	x	x		x	
Decisional Conflict scale	x	x		x	
Cognitive performance level		x			
CSSRI	x	x	x	x	x
Preparation of the return through the hospital		x			
Preparation of the return through the employer		x			
Preparation of the return through the RTW expert (intervention group only)		x		x	
Questions on the existing help network		x		x	x
Content of the employer support				x	
Evaluation of the employer support				x	
Evaluation of the RTW expert support (intervention group only)				x	
EuroQOL - Gesundheitsbarometer	x	x		x	
EQ-5D		x		x	x
Self-efficacy expectation (RTW-SE)		x			
Resilience (RS-13)					x
Patient Health Questionnaire (PHQ-D)		x			
Days at work			x	x	x
Days of incapacity for work			x	x	x
Days of partial return to work			x	x	x
Questions on discrimination at the workplace				x	
Coping				x	
Attending physician					
CGI	x	x			x
GAF	x	x			x
ICD Diagnosis and medical history	x	x			x
HoNOS		x			
Prediction on return to work		x			
RTW expert (intervention group only)					
Type and scope of workplace-related support		x		x	
Evaluation of workplace-related support		x		x	
Prediction on return to work		x			
Quality of relationship		x		x	
Return to work				x	
Questions concerning the use of communication media				x	
Open summary				x	

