#### Secondary outcomes

As outlined above an improved return to work following an in-patient psychiatric care treatment of patients may also result in a shorter period of **time to return to work** (partial/full), lower **termination rates** (both sides), a higher **quality of life** (EQ-5D, [20]), a higher **social functional level** (Mini-ICF-APP, [21]; Global Assessment of Functioning (GAF), [22]), a higher **job satisfaction** (German version of the Copenhagen psychosocial questionnaire (COPSOQ), [23]), a different **perception of stigmatization** (Self-stigma of mental illness scale – short form – subscale self-concurrence, [24]; Cognitive appraisal of stigma-related stress, [25]), lower **decisional conflict in regard to disclosure of the mental illness** (Decisional conflict Scale, [26]) and probable reduced **relapse rates**.

The basis for estimating the **cost of the illness** and the **health economic evaluation** of the RTW intervention are the medical and psychosocial health services made use of by the subjects and the number of days of incapacity for work for the whole study period.

The days of incapacity to work of the patients are on the one hand directly requested by the patients and their practitioners. It is envisaged that the patient’s details will be checked against those of some health insurance companies in order to assess the extent to which the data match.

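### The reason given for having no blinding does not cover the analyst or the staff who handle the follow-up work-day data; both could be masked at little cost

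*Protocol article*

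**What the plan says.** Under Randomization and blinding, the article says: "As to the nature of the intervention (implementation of RTW-experts) there will be no blinding". The nature of the intervention is the only reason offered. The statement covers every role, and no other section makes an exception for data collection or analysis.

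The primary objective is a group difference "using days in work and days of incapacity to work during 1 year after discharge from hospital". The statistical section narrows this to one comparison: "The primary analysis will be a comparison of days in work at T4 between the intervention and control groups".

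On sources, Table 1 lists days at work, days of incapacity and days of partial return under the patient at T2, T3 and T4, for both arms. For incapacity days the Secondary outcomes section adds: "The days of incapacity to work of the patients are on the one hand directly requested by the patients and their practitioners". Patients' details are to be "checked against those of some health insurance companies in order to assess the extent to which the data match".

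The Data collection section says: "The same data at the same time points will be collected in the intervention and control group (Table 1". Table 1 itself contains a block headed "RTW expert (intervention group only", which includes a return-to-work item at T3. It also has two patient items at T3 that are marked for the intervention group only: preparation of the return through the RTW expert, and evaluation of the expert's support.

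**The concern.** Blinding is decided role by role. That the intervention is visible to those who deliver or receive it is a good reason not to blind them. It is no reason to leave the analyst, or the people who record and code the outcome, aware of the arm.

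This matters because the primary outcome is a count of days reported by patients who know whether they had an RTW expert. Such counts need decisions: how to code partial return, what to do when incapacity days and work days do not add up, and how to treat incomplete answers. With an expected drop-out of 30 to 40%, incomplete data will be common. Decisions made with the arm known can lean one way without anyone intending it. Masking these later steps is one of the few protections still open in a trial where patients and staff cannot be blinded.

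Two features of Table 1 make a safeguard worth writing down. At T3 the intervention-only patient items reveal the arm to anyone who handles them together with the work-day answers. At the same visit the person delivering the intervention reports on return to work, with no counterpart among controls.

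**Working it through.** This is a point of reasoning from the text, so the passages are set side by side.

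**1. How far does the stated reason reach?**

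| Role | Does the nature of the intervention prevent masking? | Masked anywhere in the article? |
|---|---|---|
| RTW experts | Yes, they deliver it | No |
| Ward staff | Yes, the experts work with them on the ward | No |
| Patients | Yes in practice, once they have met the expert | Only in part: at consent they are not told of randomization or of the intervention condition |
| Staff collecting or coding T2 to T4 work days | No, these data arise after discharge | No |
| Analyst | No | No |

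The reason covers the first three rows and the decision covers all five. The article makes a positive decision here, so this is not a detail that a condensed article leaves to a fuller document.

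**2. Where does the primary outcome come from?** Table 1 places days at work under the patient, at T2, T3 and T4, in both arms. The sentence about practitioners concerns incapacity days only. The insurer check follows that sentence, involves some insurers, and aims to see how far the data match. The article does not say that it corrects the outcome.

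**3. Where would the arm be revealed?** Table 1 has no intervention-only item at T2 or T4. At T3 it has the two patient items and the RTW-expert block. The order and separation of forms therefore matter mainly at T3.

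**4. Does the RTW expert's report enter an outcome?** No section says so. In Table 1 it sits beside scope of support, quality of the relationship and an open summary, which reads as process documentation. No section rules the use out either.

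**5. Can the analyst be masked under the planned model?** Yes, with two precautions. The per-protocol rule requires one inpatient contact and one contact after discharge with the RTW expert, and it applies to intervention patients only. Anyone who applies it sees the arm, so the set has to be flagged by someone else beforehand. The model has ward as a random effect, so wards also need neutral codes.

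**6. Does the change affect the sample size?** The plan's figure reproduces. For an effect size of 0.5, two-sided α = 0.05 and 80% power, the exact two-sample t-test needs 63.77, so 64 per arm, and 2 × 64 = 128 (power 0.801). Adding the planned 72 gives 128 + 72 = 200. Masking enters neither step, so both figures stand.

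**The case against.** The strongest reply is that this is an openly declared and common choice in a pragmatic ward-level trial, and that masking would miss the main route of bias. Patients report the days and know what support they had; a masked collector cannot change that. This stands, and it limits what the fix can achieve.

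The plan also has protections of its own. Patients are not told about randomization at consent, wards share no personnel, incapacity days are compared with some insurers' data, and the primary model is fixed in advance, which narrows the analyst's discretion. These reduce the risk but mask nobody who handles the follow-up data.

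A reader might infer several stronger points that the documents do not support:

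- *The RTW expert is a second outcome source in one arm, so outcome availability differs by arm.* The day counts are patient items in both arms, and no section uses the expert's T3 report to fill or correct them. That report also comes at 6 months, while the outcome runs to 12.
- *Practitioners supply the primary outcome.* The practitioner source is stated for incapacity days, while the primary analysis compares days in work.
- *Interviewers collect the work days.* The article does not say whether the forms are completed by interview or by the patient. If patients complete them alone, masking applies to those who code and reconcile the answers.
- *Global Assessment of Functioning (GAF) and Clinical Global Impression (CGI) ratings at T4 come from the treating ward.* Table 1 names the attending physician, and nothing says that this physician, a year after discharge, belongs to the index ward. Outside raters might also need extra staff.
- *Table 1 contradicts the statement that the same data are collected in both arms.* That sentence cites the table, which labels the exceptions, and controls cannot rate an expert they never had.

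**Conclusion.** The point holds in a limited form. The only reason given for having no blinding does not extend to the analyst or to the staff who handle T2 to T4 work-day data, and nothing else in the article masks them. The gap concerns a primary outcome reported by unblinded patients, so the protection is worth having.

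It is a risk and not a demonstrated bias. No numerical size is offered: the documents give neither the mean and spread of days at work nor any measure of differential reporting, and any figure would mix patient over-reporting, which masking cannot remove, with coding choices, which it can. The conclusion assumes only that someone other than the ward team and the RTW expert can code and analyse the data. Study staffing is not described, so masking of collectors is conditional on it, while masking of the analyst is not. This is a cheap improvement that should be made; it does not by itself undermine the trial.

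**What to change.** Replace the blinding sentence with: *Patients, ward staff and RTW experts are not blinded. The analyst works on masked arm codes, with the per-protocol set flagged beforehand by someone else. Staff who collect or code T2 to T4 work days are masked to arm where existing staffing allows, and any unmasking is recorded.* Give wards neutral codes in the analysis file.

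In addition:

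- Ask days at work, incapacity days and days of partial return before any intervention-only item, and move those items to a separate form completed afterwards.
- State that the RTW expert's T3 report on return to work is process data and is never used to set, correct or impute an outcome.
- Report the agreement between self-reported and insurer data separately by arm. This is the one planned check that could show differential reporting, though it covers incapacity days and some insurers only.

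The cost is wording, a re-ordered T3 form and a coded analysis file. The sample size does not change. Two limits should be stated openly: some patients will reveal their arm to collectors, and bias in the patients' own reports remains.
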